## Abstract

**Background:**

Type 2 diabetes is a significant cause of morbidity and mortality in the United States. Lifestyle modifications including increasing physical activity and losing weight have been demonstrated to improve glycemic control. However, most patients struggle to make these changes. Many stakeholders are interested in using gamification and social incentives to increase engagement in healthy behaviors. However, these approaches often do not appropriately leverage insights from behavioral economics that could be used to address predictable barriers to behavior change.

**Objective:**

This study aimed to describe the protocol for the *Influencing DIabetics to Adapt Behaviors related to Exercise and weighT by Enhancing Social incentives* (iDiabetes) trial, which aimed to evaluate the effectiveness of gamification interventions that leverage insights from behavioral economics to enhance supportive, competitive, or collaborative social incentives to improve glycemic control, promote weight loss, and increase physical activity among overweight and obese adults with type 2 diabetes.

**Methods:**

We are conducting a one-year four-arm randomized controlled trial of 361 overweight and obese patients with type 2 diabetes and a glycated hemoglobin (HbA_1c_) level ≥8.0. Wireless weight scales and wearable devices are provided to remotely monitor weight and physical activity and transmit data to the study team. Patients are recruited by email, following which they establish a baseline measure of weight, daily step count, HbA_1c_ level, and low-density lipoprotein cholesterol level and then repeat these measures at 6 and 12 months. The control arm receives no other interventions. Patients randomized to one of the three intervention arms are entered into a game designed using insights from behavioral economics to enhance supportive, competitive, or collaborative social incentives. To examine predictors of strong or poor performance, participants completed validated questionnaires on a range of areas including their personality, risk preferences, and social network.

**Results:**

Enrollment of 361 patients was completed in January 2019. Results are expected in 2020.

**Conclusions:**

The iDiabetes trial represents a scalable model to remotely monitor the daily health behaviors of adults with type 2 diabetes. Results from this trial will help provide insights into how to improve management of patients with type 2 diabetes.

**Trial Registration:**

ClinicalTrials.gov NCT02961192; https://clinicaltrials.gov/ct2/show/NCT02961192

**International Registered Report Identifier (IRRID):**

DERR1-10.2196/14180

## Introduction

### Background

Type 2 diabetes is a significant cause of morbidity and mortality in the United States [1,2]. Lifestyle modifications including increasing physical activity and losing weight have been demonstrated to improve glycemic control [3,4]. However, changing daily health behaviors can be challenging for many patients, especially those who start with lower levels of motivation. Recently, many stakeholders have become interested in using mobile technologies to passively monitor these daily behaviors and to deploy interventions at a broader scale [5,6].

Gamification is the use of game design elements in nongame settings and is increasingly being used in interventions to promote healthy behaviors [7]. Although gamification is used widely, it is often not designed to incorporate theories from health behavior [8-11]. Behavioral economics is a field that incorporates principles from psychology and economics to help us understand why individuals make decisions that are predictably irrational [12,13]. For example, individuals tend to be more motivated to avoid losses than gain an equivalent reward [14-16], by immediate rather than delayed gratification [17], and they tend to avoid the feeling of regret [18]. In a randomized trial, members of our group found that insights from behavioral economics could be embedded within gamification design to enhance social incentives such as accountability, peer support, and collaboration to significantly increase physical activity among families in the community [19]. We have also conducted a pilot study to demonstrate how these approaches could be used to promote weight loss [20].

### Objective

The objective of this article was to describe the protocol for the *Influencing DIabetics to Adapt Behaviors related to Exercise and weighT by Enhancing Social incentives* (iDiabetes) trial, which aimed to evaluate the effectiveness of gamification interventions that leverage insights from behavioral economics to enhance either supportive, competitive, or collaborative social incentives to improve glycemic control, promote weight loss, and increase physical activity among overweight and obese adults with type 2 diabetes. This builds upon on our previous work by testing more types of social incentives and implementing them with a more high-risk population. The trial recruited patients from Penn Medicine, an academic health system in Philadelphia, and used a Web-based platform at the University of Pennsylvania, called Way to Health [21], which facilitated virtual recruitment, Web-based informed consent, automated study communication, and remote monitoring of behavior.

## Methods

### Study Design

iDiabetes is a 4-arm randomized controlled trial with a 1-year intervention period. The trial was conducted using Way to Health [21], an automated information technology platform at the University of Pennsylvania that integrates wireless devices, conducts clinical trial randomization and enrollment processes, delivers messaging (via text or email), delivers self-administered surveys, automates payment transfers, and securely captures data for research purposes. This platform has been used to run over 100 clinical trials including several by our group focusing on physical activity and weight loss [8,15,16,19,20,22-25]. All participants received US $25 for completing laboratory testing to assess baseline hemoglobin A1c (HbA_1c_) and low-density lipoprotein cholesterol (LDL-C) during the enrollment process. Participants who were eligible and completed enrollment into the study received an additional US $25. Participants received US $50 to obtain laboratory tests (HbA_1c_ and LDL-C) and conduct a virtual weigh-in at home via FaceTime (Apple Inc.) or Skype (Microsoft Inc) after 6 months and 12 months, similar to prior work [20]. Participants were randomly assigned to the control arm or 1 of 3 gamification intervention arms designed to enhance supportive, competitive, or collaborative social incentives. Data on participant characteristics were collected through validated questionnaires. The University of Pennsylvania Institutional Review Board approved the study.

### Participant Recruitment

Potential participants were identified from EPIC, the electronic health record at Penn Medicine, by using Penn Data Store (the health system’s clinical data warehouse) and Clarity, an EPIC reporting database. The study team sent email invitations, letters, and made phone calls introducing the study and its eligibility criteria with instructions on how to learn more and begin the enrollment process online. Recruitment occurred from January 23, 2017, to January 7, 2019.

Participants were eligible for the program if they were aged between 18 and 70 years, they were able to read and provide informed consent to participate, they had a diagnosis of type 2 diabetes with an HbA_1c_ level of 8.0 or greater within the last 90 days, they had a self-reported body mass index of 25 or greater, and they owned a smartphone or tablet compatible with the wearable device and wireless weight scale. Participants were excluded if there was a condition that made their participation unfeasible (eg, inability to provide informed consent and illiteracy or inability to speak, read, and write English), if there was a condition that made participation unsafe (eg, pregnancy, previous diagnosis of an eating disorder, or history of unsafe weight loss practices), or if he or she was already enrolled in another study targeting physical activity, weight loss, or glycemic control or any other medical conditions or reasons because of which the participant would be unable to complete the 1-year program.

### Participant Enrollment

Interested participants were instructed to visit the study website to create an account, review and complete informed consent, and complete the eligibility survey. Eligible participants who had not recently had blood tests were then instructed to obtain baseline HbA_1c_ and LDL-C laboratory tests that were conducted at either a qualifying Penn Medicine facility or a Quest Diagnostics laboratory. Participants were also instructed to complete a series of assessments including surveys and validated questionnaires described in Table 1. These included a baseline survey assessing sociodemographic and health characteristics, the domain-specific risk-tasking survey collecting data related to risk preferences [26], personality type (Big Five Inventory) [27], and the Medical Outcomes Study Social Support survey [28]. The qualitative assessment at the end of the study is conducted through an online survey and participants are asked to rate their satisfaction with the devices, interventions, and study overall by using Likert scales (strongly agree, agree, neutral, disagree, and strongly disagree). Participants are also asked to respond to open-ended prompts to describe ways in which their experience helped or did not help them to lose weight, increase physical activity, and manage their diabetes.

After baseline assessments were completed, participants were mailed a wearable device (Withings Steel) and were given instructions on how to authorize the device to send data to the Way to Health technology platform (Figure 1). This wearable device tracked physical activity (daily step count) and sleep (minutes of total sleep, light sleep, and deep sleep). These types of devices have been demonstrated by our previous study to be accurate for tracking step counts [29]. The wearable device was waterproof and had a battery that lasted about 6 months. Participants were provided with a replacement battery at the beginning of the study and, if necessary, were mailed a new battery later. The study team was available on phone to help participants set up the wearable device.

**Table 1 table1:** Participant survey assessments.

Domain	Questionnaire	Questions (n)	Baseline	6 months	12 months
Baseline	—^a^	—	✓	—	—
Social support	Medical outcomes study social support	19	✓	—	—
Risk preferences	Domain-specific risk-tasking survey	30	✓	—	—
Personality	Big Five	44	✓	—	—
Qualitative survey	—	—	—	—	✓

^a^Not applicable.

**Figure 1 figure1:**
[figure not shown]
Depiction of the wireless devices used by participants.

### Baseline Step Count

Once the participants’ wearable device was setup and connected to the study, they were asked to get used to wearing the device for several weeks. During this period, a baseline step count was estimated using the second week of data—a method used in previous work [16,19]. The first week of data was ignored to diminish the potential upward bias of the estimate from higher activity during initial device use. To prevent potential mismeasurement, we ignored any daily values less than 1000 steps because evidence indicates that these values are unlikely to represent capture of the actual activity [30,31]. If less than 4 days of data were available during the second week, the patient was contacted to inquire about any device issues, and the run-in period was expanded until at least four days of data were captured.

### In-Person Visit and Randomization

After a baseline step count had been established, the participant was scheduled for an in-person visit with the study team to complete the enrollment process. During this visit, all participants received education on the importance of diet and physical activity for weight loss and glycemic control. The participants were provided with a wireless weight scale and had a baseline weight measured (Figure 1). As weight can fluctuate based on time of day and clothing, we monitored for weights taken at home that were >5 lbs different. In those cases, the study team reached out to participants to clarify the most accurate weight to use as his or her baseline. At the in-person visit, participants were then randomized to one of the study arms. A participant was considered ready to be randomized once he or she had completed all surveys, established a baseline step count, completed baseline laboratory work for HbA_1c_ and LDL-C, and had come in for an in-person study visit to establish a baseline weight measurement. Randomization was conducted electronically using block sizes of 4 groups with 3 participants per group. The first participant in the group was randomly assigned to an arm, and the next 2 participants were assigned to fill that group. In most cases, the participants in a group did not previously know each other. However, if 2 participants did know each other and wanted to join together, then they were randomized together as either groups of 2 or 3 persons. Participants were informed of their arm assignment during the in-person visit with the opportunity to ask any questions related to the intervention design.

All investigators, statisticians, and data analysts were blinded to arm assignments until the study and analysis were completed.

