### Interventions

Participants in the control arm used the devices but received no other interventions and were not asked to conduct goal setting. Participants randomized to 1 of the 3 gamification arms conducted goal setting during the in-person visit. This included selecting a HbA_1c_ reduction goal (1.5%, 2%, or 2.5%), a weight loss goal (6%, 7%, or 8% of their baseline weight), or an increase in daily step counts (33%, 40%, or 50% greater than baseline, or any step goal that is at least 1500 steps above their baseline). A number of design considerations were incorporated to help participants achieve their goals while minimizing risks. First, the weight loss goal was set for a gradual decline over the first 26 weeks and then to maintain that level during the next 26 weeks. Participants were given a weight target each week, and if not achieved, the target remained the same for the following week. Second, participants had a 4-week ramp up toward their daily step goal. For example, a participant with a baseline of 6000 steps per day and goal of 8000 steps per day was asked to achieve goals of 6500, 7000, 7500, and 8000 for each of the first 4 weeks of the study. Then, they were asked to maintain the 8000 steps per day goal for the remainder of the study. Finally, the HbA_1c_ goal was set for the 6-month time point and was expected to be maintained through 1 year.

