Participants in the gamification arms were entered into an intervention approach based on prior work that used points and levels designed to incorporate insights from behavioral economics [19,20]. First, participants were asked to sign a precommitment pledge to strive to achieve their goals during the study. Precommitment has been demonstrated to motivate behavior change [32,33]. Second, at the beginning of each week, the participant received 70 points (10 for each day that week). If the participant did not weigh-in, they lost 10 points from their balance. This leverages loss aversion, which has demonstrated that loss framing is more effective at motivating behavior change than gain framing [14-16]. Third, at the end of each week, if participants had at least 40 points, achieved their weekly weight target, and averaged at or above their daily step goal, they were moved up a level (levels from lowest to highest: blue, bronze, silver, gold, and platinum). If not, participants were dropped a level. This design creates achievable goal gradients—the notion that the next highest level was attainable—and a sense of social status and progression through the game. All participants begin at the silver level, so that they will feel the loss of dropping to bronze if they do not achieve enough points in the first week. Participants who finished in the platinum level received a trophy, and participants who finished in the gold level received a medal. Fourth, participants got a new set of 70 points every Monday. This design leverages the *fresh start effect* that is the tendency for aspirational behavior around temporal landmarks such as the beginning of the year, month, or week [34]. Fifth, to help re-engage participants who are struggling to meet their goals at months 3, 6, and 9 (defined as being in the blue or bronze levels of the game), the study coordinators called them to inquire about their progress in the study, reset them to the silver level, and offered them the opportunity to readjust their goals based on their initial options. Sixth, the participants’ primary care physician was mailed a monthly report with data on their change in weight, step goals, HbA_1c_, and LDL-C (Figure 2). A copy of this letter was also mailed to the participant. Finally, the game varied based on the social incentive arm described as follows:

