### Outcome Measures

The primary outcomes were change in HbA_1c_, change in weight in pounds, and change in mean daily steps from baseline to the end of the 1-year study. Secondary outcomes include the change in LDL-C levels from baseline to end of the 1-year study, and change in mean daily steps, weight in pounds, and HbA_1c_ from baseline to the 6-month time point of the study.

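### Baseline weight can be replaced using home weights that come after randomization, with a participant who knows the arm, so the primary weight contrast can be biased in either direction

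*Protocol article*

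**What the plan says.** Under Participant Enrollment, only the wearable device is mailed out before the visit. Under In-Person Visit and Randomization, the scale and the baseline weighing come at the visit: "The participants were provided with a wireless weight scale and had a baseline weight measured". Because weight varies with clothing and time of day, the team then checked home readings: "we monitored for weights taken at home that were >5 lbs different". The article gives this consequence when such a difference was found: "In those cases, the study team reached out to participants to clarify the most accurate weight to use as his or her baseline".

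Randomization takes place at the same visit, and a baseline weight obtained there is one of the conditions for it. Disclosure follows at once: "Participants were informed of their arm assignment during the in-person visit". The blinding statement in that section covers investigators, statisticians and data analysts. It mentions neither participants nor the staff who contacted them.

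Under Interventions, gamification participants choose among goals that include "a weight loss goal (6%, 7%, or 8% of their baseline weight", and weekly weight targets follow. The general game rule on weigh-ins is: "If the participant did not weigh-in, they lost 10 points from their balance". Control participants use the devices but set no goals and play no game.

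Under Outcome Measures, weight change over one year is among three primary endpoints: "The primary outcomes were change in HbA_1c_, change in weight in pounds, and change in mean daily steps from baseline to the end". Weight change to 6 months is secondary. Under Statistical Analysis, the primary model adjusts for each participant's baseline value.

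**The concern.** A baseline protects a randomized comparison because it is fixed before assignment and so cannot depend on the arm. Here the value can be changed after assignment, in a conversation with someone who knows the arm, and the events that prompt the conversation need not be equally common across arms.

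Three routes to an imbalance follow from the text:

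- **Number of readings.** Gamification participants have a reason to step on the scale that control participants lack, so they may produce more home readings that can cross the 5-lb threshold.
- **Stake in the value.** A higher baseline makes a percentage-based target easier to meet. Control participants have no target.
- **Real change.** A true early loss of more than 5 lb could trigger the rule. If the lower value then became the baseline, part of the treatment effect would be absorbed into it.

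The second route would exaggerate benefit and the third would hide it. The first has no fixed sign. Adjusting for baseline does not remove the problem, because the covariate is then the value that may depend on arm.

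**Working it through.** **Step 1: order of events.** Setting Participant Enrollment beside In-Person Visit and Randomization gives: wearable mailed; step baseline established; in-person visit with scale provided, weight measured, arm assigned and arm disclosed; then weighing at home. The sentence on checking home weights is printed before the sentence on randomization. Since the study scale is first provided at the visit, however, home readings on it must follow the visit. The order is inferred, but firmly.

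**Step 2: the plan's own weight figure.** Inputs from the Power section: 90 per arm, 10% dropout, SD 10 lb, difference 6 lb, two-sided alpha 0.017.

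- Evaluable per arm: 90 x 0.9 = 81.
- SE of an arm difference: 10 x sqrt(2/81) = 1.57 lb.
- Critical value for two-sided 0.017: 2.387, which is a difference of 2.387 x 1.57 = 3.75 lb.
- Power: Phi(6/1.571 - 2.387) = Phi(1.43) = 92.4% (91.9% with the t distribution).

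The stated figure of at least 80% is reproduced. The point disputes no sample-size figure.

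**Step 3: how a revision reaches the contrast.** Let f be the net directional excess share of participants revised in an intervention arm compared with control, and m the mean shift in lb. The mean baseline difference moves by f x m. In a linear model adjusted for baseline, the treatment contrast is the same whether the outcome is change or final weight, so the shift acts once, multiplied by the slope of final weight on baseline. Taking that slope as about 1 (an assumption, plausible for weight), bias = f x m.

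**Step 4: illustrative values.** f and m are assumed, since the article reports neither. Type I error for one comparison with no true effect is Phi(-2.387 + b/1.571) + Phi(-2.387 - b/1.571), where b is the bias.

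| f | m (lb) | Bias (lb) | Share of 6 lb | Type I error (nominal 0.017) |
|---|---|---|---|---|
| 0 (balanced) | any | 0 | 0% | 0.017 |
| 5% | 5 | 0.25 | 4% | 0.018 |
| 10% | 5 | 0.5 | 8% | 0.023 |
| 20% | 5 | 1.0 | 17% | 0.041 |
| 30% | 7 | 2.1 | 35% | 0.147 |

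The last row shows what an extreme imbalance would do. Nothing in the article suggests that it occurred.

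**The case against.** The strongest reply is that the rule corrects measurement error: the reason given is clothing and time of day, and follow-up weigh-ins are also done at home, so a home weight is the closer match. That is a fair reason to want the corrected value, but not for letting a value settled after assignment serve as the primary baseline. A clothing offset in a weight taken before assignment is independent of arm and cancels in expectation from the contrast.

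Four further objections stand, and they limit the point:

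- **Staff knowledge.** A reader might infer that whoever made the call also knew the arm. The article does not say who made it. Only the participant's knowledge is documented.
- **Weigh-in incentive.** A reader might infer that every gamification participant loses points for each missed day. In the collaborative arm, points are lost only if the member selected for that day missed the weigh-in. The team rule for moving up also mentions only the points threshold, so the pull from the weight target is less certain there.
- **Strength and direction.** The game rewards are a trophy or medal, and the payments are not tied to weight lost. Lighter clothing at home would tend to lower the baseline, against the incentive to raise it. The net direction cannot be predicted.
- **Condensed detail.** The time window and the criterion for choosing a weight may be in the full protocol, so their absence here is not counted as a fault. The point rests on the revision rule that the article does state.

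**Conclusion.** The point holds as a risk of bias. The stated procedure lets the baseline of a primary outcome be replaced after randomization, in discussion with a participant who knows the arm, while the pressures on that value differ between the gamification arms and control.

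The size is unknown. It is roughly the net directional excess share revised times the shift: 0 if revisions are balanced, and 0.25, 0.5 or 1.0 lb at 5%, 10% or 20% with a 5-lb shift, against a planned 6 lb. These figures rest on assumed shares and shifts and on a baseline slope near 1.

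A reader might go further and infer that the weight result is biased in favour of gamification, or that the error is a large part of the planned effect. The article supports neither inference: it gives no number, direction or arm split of revisions. Nor does using baseline both in the change score and as a covariate double the effect, because it acts once on the adjusted contrast.

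**What to change.** State in the analysis plan that, for the primary 12-month and secondary 6-month weight analyses, baseline is the weight measured at the in-person visit before randomization, for every participant. Keep any clarified weight out of the primary analysis. Report the number and direction of revisions by arm, and give the analysis with revised baselines as a sensitivity analysis.

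The cost is small. A visit weight was a condition of randomization, so one was taken for everyone, and the sample size and planned power figures do not change. Clothing and time-of-day noise stays in the baseline, and the visit weight is less like-for-like with home follow-up. Both slightly lower precision, but neither depends on arm. The fix also requires that the original visit value was kept when a baseline was replaced. The article does not say so, and this should be confirmed before unblinding. If some values were overwritten, report how many in each arm.
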